### 2.4. Randomization and Allocation Concealment

Following eligibility assessment and baseline evaluations, participants will be randomly assigned to either the experimental group or the control group in a 1:1 ratio. Randomization will be performed using a centralized computer-based randomization system (Sealed Envelope™, London, UK; https://www.sealedenvelope.com). A block randomization procedure with randomly varying block sizes will be used to maintain balance between groups while preserving allocation unpredictability. In view of the expected sample size, stratified randomization will be performed by sex and age, ensuring balanced allocation of both variables across the experimental and control groups.

The allocation sequence will be generated by a researcher not involved in participant recruitment, baseline assessments, intervention delivery, or outcome evaluation. The investigators responsible for recruitment and baseline assessments will remain blinded to the allocation sequence and block sizes until participants have been enrolled and baseline measurements have been completed. Once assigned, group allocation will not be modified throughout the intervention period.

### 2.5. Blinding

Due to the nature of the exercise intervention, participants, families, and trainers cannot be blinded to group allocation. However, outcome assessors will be blinded to group allocation during baseline and post-intervention assessments. Participants and families will be instructed not to disclose their group allocation to the assessors during the post-intervention evaluations. Data analysis will be performed using coded group labels whenever feasible to reduce analytical bias.

### 2.6. Control of Contamination and Lifestyle-Related Factors

Because participants will be recruited from the same school, families in both groups will be asked to maintain their children’s usual routines during the intervention period. Control-group participants will be asked not to start any new structured exercise programme during the study. Likewise, families in the experimental group will be asked to avoid additional structured training outside the intervention.

Although diet, sleep, spontaneous physical activity, and screen time will not be objectively monitored, families will be asked to avoid intentional changes in these habits during the intervention period. Any relevant change in extracurricular physical activity, diet, sleep routines, or screen time reported by families will be recorded descriptively and considered when interpreting the results.

### 2.7. Ethical and Legal Aspects

The present study protocol was registered at ClinicalTrials.gov under the identifier NCT07552844 and approved by the Córdoba Research Ethics Committee (IMIBIC, Córdoba, Spain) under protocol code SICEIA-2025-000408. The study will be conducted in accordance with the ethical principles of the Declaration of Helsinki (World Medical Association, 2013), [27] the principles of Good Clinical Practice (ICH-GCP), [28] and the current Spanish and European legislation governing biomedical research involving human participants, including Law 14/2007 of 3 July on Biomedical Research [29], Royal Decree 1090/2015 regulating clinical trials with medicinal products (if applicable) [30], Regulation (EU) 2016/679 of the European Parliament and of the Council (General Data Protection Regulation) [31], and Organic Law 3/2018 of 5 December on Personal Data Protection and Guarantee of Digital Rights [32].

Before participation, parents or legal guardians will receive detailed written and verbal information regarding the study aims, procedures, potential benefits, and possible risks associated with participation. Written informed consent signed by parents or legal guardians will be required prior to enrollment. Participation in the study will be completely voluntary, and participants may withdraw from the study at any time without consequences.

Participant confidentiality and anonymity will be strictly guaranteed throughout the entire research process. All collected data will be anonymized and codified using numerical identification codes to prevent participant identification. Only the research team will have access to the study data, which will be securely stored and protected from unauthorized access in accordance with current data protection regulations. Coaches, teachers, and non-research staff will not have access to individual participant information or study results.

In accordance with Spanish data protection legislation, parents or legal guardians of participants under 14 years of age may exercise the rights of access, rectification, erasure, restriction of processing, data portability, and opposition concerning the personal data of the participants. Any request related to these rights may be addressed directly to the research team.

All intervention sessions and assessment procedures will be supervised by qualified professionals specialized in pediatric physical exercise and HIFCT in order to ensure participant safety and minimize the risk of injury during exercise practice. In addition, the study will follow quality assurance and Good Clinical Practice procedures throughout all phases of the research process. Before the start of the intervention, all professionals involved in programme delivery will be familiarized with the study protocol, session structure, exercise progressions, and safety procedures to ensure standardized implementation.

### 2.8. Procedures

#### 2.8.1. Training for Researchers

Before the beginning of the study, all researchers and exercise professionals involved in the intervention and assessment procedures will participate in a standardized training session. The training will focus on the correct administration of physical fitness tests, anthropometric measurements, and psychological questionnaires in order to ensure consistency and reliability across all assessments. Special attention will be given to the standardization of testing procedures, participant safety, exercise supervision, and data collection protocols. In addition, the research team will review the correct use of all assessment equipment and the procedures established for the intervention sessions.

#### 2.8.2. Intervention

The intervention programme will last 8 weeks and will consist of two weekly sessions of approximately 50 min each. Participants assigned to the experimental group will complete a supervised HIFCT programme specifically adapted to the age and physical capacities of school-aged children. Training sessions will be conducted at Triple XXX CrossFit facilities (Córdoba, Spain) and supervised by professionals specialized in pediatric physical exercise and HIFCT to ensure participant safety, correct exercise execution, and injury prevention. Each session will include HIFCT exercises combining strength, coordination, balance, and cardiorespiratory conditioning using age-adapted equipment such as plyometric boxes, rowing and ski ergometers, skipping ropes, medicine balls, and body-weight exercises. The intervention program will be structured into four main sections: (i) warm-up; (ii) strength training; (iii) metabolic conditioning (METCON); and (iv) cool-down activities (Table 1) [33]. Sessions will incorporate greater movement complexity, longer work intervals, progressive introduction of light external loads (medicine balls, resistance bands) from week 3 onwards, and a higher training density consistent with their greater attentional capacity and motor maturity. This differentiation is consistent with the Youth Physical Development model and current long-term athletic development frameworks, which recommend that training content be tailored to developmental stage rather than chronological age alone [20,21].

The warm-up phase (15 min) will include mobility exercises and dynamic games aimed at increasing body temperature and preparing participants for exercise. The strength block (15 min) will focus on movement technique and age-adapted strength exercises. The METCON component (10 min) will consist of functional circuits performed at moderate-to-vigorous intensity, combining aerobic and muscular endurance exercises. Finally, the cool-down phase (5–10 min) will include games, mobility exercises, and recovery activities [20] (Table 2). Exercise sessions will be performed at a target moderate-to-vigorous intensity. Session density will be standardized through the fixed structure described above. Work-to-rest ratios will vary according to the objectives and characteristics of each session, ranging from continuous AMRAP formats to circuit-based activities incorporating recovery periods of approximately 30–60 s between rounds.

Internal training load and perceived exercise intensity will be monitored after each session using the Pictorial Children’s Effort Rating Table (PCERT) [34], allowing training demands to be adjusted when necessary. Training load will be progressively increased throughout the intervention by manipulating exercise volume (number of repetitions and rounds), movement complexity, external resistance when appropriate, and work-to-rest ratios, while maintaining age-appropriate exercise demands and correct movement execution. The progression strategy implemented across the 8-week intervention is summarized in Table 1. Exercises will be individually adapted according to participants’ motor competence, physical fitness level, technical proficiency, and developmental characteristics. Coaches will apply a three-stage progression model for teaching movement patterns: (i) movement exploration and body awareness; (ii) technique instruction through verbal cues, visual demonstration, and manual guidance; and (iii) technique consolidation under supervised low-complexity practice. Progression to higher-complexity or loaded variations will only occur once correct execution of the fundamental pattern has been confirmed by the supervising coach. Adaptations may include modifications to exercise complexity, range of motion, movement execution, training volume, or recovery periods to ensure safe and appropriate participation. Attendance will be recorded at every training session. Participants attending at least 80% of the scheduled sessions will be considered adherent to the intervention protocol. Any missed sessions and the reasons for absence will also be documented throughout the study period.

Exercise selection, movement complexity, external loading, METCON duration, and work density will be adapted according to age, motor competence, and technical proficiency. Adaptations may include modifications to exercise complexity, range of motion, movement execution, training volume, or recovery periods to ensure safe and appropriate participation.

The volume and intensity of each session will be designed in accordance with current recommendations for youth resistance and neuromuscular training in untrained school-aged children. The NSCA recommends that beginners start with 1 set of 10–15 repetitions per exercise, progressing gradually to 1–3 sets of 6–15 repetitions as technical proficiency and tolerance develop [20]. Accordingly, the strength component of the intervention will generally be prescribed within a range of 2–3 sets per exercise across the programme, with exercise complexity, external loading, and selected training volumes progressed according to technical competency, session objectives, and individual tolerance. In parallel, the volume and density of jumping tasks and METCON activities will be prescribed conservatively and progressively adjusted across the intervention. During the initial sessions, lower-complexity jumping tasks, moderate jump density, and shorter METCON formats will be prioritised, whereas more demanding jumping variations and longer conditioning blocks will be introduced progressively in the later sessions when the supervising coach confirms adequate movement control, landing mechanics, and tolerance to training load. Thus, higher-impact variations such as tuck jumps or jump lunges will be delayed, simplified, or replaced whenever they are considered inappropriate for the participant’s technical competency or fatigue level. Internal load will be monitored after each session using the PCERT [34], and the supervising coach will be allowed to reduce exercise volume, movement complexity, work density, or introduce brief intra-session pauses whenever a session is considered excessively demanding for the participant’s competency or fatigue level.

Exercise progression will follow a competency-based approach, whereby progression to more technically demanding or externally loaded exercises will only occur after participants demonstrate adequate movement quality and postural control during prerequisite tasks. Initial training will emphasize bodyweight exercises, unloaded movement patterns, elastic-band exercises, and low-load medicine-ball activities. External resistance and exercise complexity will be progressively increased according to individual technical competency, as judged by the supervising coach using predefined movement-quality criteria. Jumping tasks and metabolic conditioning exercises will likewise be adapted according to movement competency, ensuring that exercise selection remains appropriate for each participant throughout the intervention. This progression model was designed according to current recommendations for youth resistance training and long-term athletic development [20,21].

An adverse event will be defined as any injury, pain, discomfort, illness, or other undesirable occurrence arising during participation in the intervention sessions. Participation may be temporarily or permanently suspended if a participant experiences a medical condition or adverse event that compromises safe participation, as determined by the research team and, when appropriate, by the participant’s healthcare provider. All training sessions will be conducted at facilities equipped with first-aid resources and supervised by qualified personnel trained to follow the standard emergency procedures established by the facility [20,21]. Participants assigned to the control group will not participate in the intervention programme and will maintain their usual daily routines throughout the study period.

Attendance will be recorded at every training session. Participants attending at least 80% of the scheduled sessions will be considered adherent to the intervention protocol. Any missed sessions and the reasons for absence will also be documented throughout the study period.

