## Abstract

High-intensity functional concurrent training (HIFCT) has emerged as a form of training characterized by constantly varied functional movements adapted to individual fitness levels. Previous studies have reported positive effects on muscular strength, cardiorespiratory fitness, body composition, and psychological well-being; however, evidence regarding HIFCT interventions in school-aged children remains limited. Therefore, the aim of the present study protocol is to evaluate the effects of an 8-week HIFCT programme on muscular strength, cardiorespiratory fitness, body composition, anxiety, stress, and self-esteem in children aged 10–12 years. Physical fitness, anthropometric variables, and psychological outcomes will be assessed before and after the intervention using validated field-based tests and questionnaires. This study may provide novel evidence regarding the feasibility, safety, and potential effects of HIFCT programmes in the school setting. The study protocol was registered at ClinicalTrials.gov (NCT07552844) and approved by the Córdoba Research Ethics Committee (IMIBIC, Córdoba, Spain; protocol code SICEIA-2025-000408).

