### 2.9. Outcomes

All outcome variables will be assessed at baseline (pre-test) and immediately after the 8-week intervention period (post-test). The study will evaluate physical fitness, body composition, and psychological outcomes in children aged 10–12 years using validated field-based tests and questionnaires (Figure S2). All baseline and post-intervention assessments will be completed during a single evaluation session lasting approximately 60–90 min. To minimize fatigue, physical fitness tests will be administered in a standardized order with adequate recovery periods between assessments according to established testing protocols. Participants will receive standardized instructions and verbal encouragement throughout the testing session. Familiarization trials will be provided when required by the testing protocol to ensure adequate understanding of the procedures and to promote valid test performance. Before the strength assessments, all participants will perform a standardized warm-up protocol consisting of: (i) a general warm-up including light running, skipping, heel-to-glute movements, arm circles, wrist and ankle rotations, lunges, and changes in direction; (ii) a specific warm-up for jump including controlled squats, low-intensity jumps, and lunges with trunk rotation; (iii) a specific warm-up for handgrip dynamometry involving squeezing a rubber ball and wrist flexion-extension exercises; and (iv) a specific warm-up for the medicine ball throw including shoulder rotations, light medicine ball throws, and core activation exercises.

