#### 2.9.1. Primary Outcome

##### VO_2_max (Course-Navette Test)

Cardiorespiratory fitness will be assessed using the 20-m Course-Navette test, a validated field-based test widely used to estimate maximal oxygen uptake (VO_2_max) in children and adolescents [35]. Participants will run continuously between two lines separated by 20 m at progressively increasing speeds, starting at 8.5 km·h^−1^ and increasing by 0.5 km·h^−1^ every minute. The test will be terminated when participants fail to reach the line in time on two consecutive occasions or voluntarily stop due to fatigue. VO_2_max will subsequently be estimated from the final stage attained using the equation developed by Léger et al. [35].

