## 4. Conclusions

This study protocol describes an 8-week HIFCT intervention designed to evaluate its feasibility, safety, and potential effects on muscular strength, cardiorespiratory fitness, body composition, and psychological outcomes in school-aged children. Considering the increasing interest in HIFCT modalities in pediatric populations, this study may provide novel evidence regarding the implementation of developmentally appropriate HIFCT programme in children aged 10–12 years.

The integration of both physical and psychological outcomes represents one of the main strengths of the present protocol and may contribute to a broader understanding of the potential effects associated with HIFCT during childhood. Furthermore, the structured and supervised nature of the intervention may provide valuable information regarding the feasibility and safety of implementing age-appropriate HIFCT strategies in school and community settings.

The findings of this study may contribute to the growing evidence base on HIFCT in pediatric populations and help inform the design of future randomized controlled trials. Nevertheless, further large-scale and long-term studies will be required to confirm the findings and establish evidence-based recommendations regarding the use of HIFCT in children and adolescents.

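### Adverse events count only if they arise in an intervention session, so the trial can describe in-session events in the experimental arm but not comparative safety or the programme's full safety

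*Protocol article*

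**What the plan says.** Section 2.8.2 (Intervention) of the protocol article gives the only definition of harm: "An adverse event will be defined as any injury, pain, discomfort, illness, or other undesirable occurrence arising during participation in the intervention sessions". The same section says of the other arm: "Participants assigned to the control group will not participate in the intervention programme and will maintain their usual daily routines throughout the study period". Exposure is also fixed there: "The intervention programme will last 8 weeks and will consist of two weekly sessions of approximately 50 min each".

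Fitness testing is separate from the sessions. Section 2.9 says: "All baseline and post-intervention assessments will be completed during a single evaluation session lasting approximately 60–90 min". The tests include a shuttle run to failure or voluntary stop ("Participants will run continuously between two lines separated by 20 m at progressively increasing speeds"), maximal jumps, a medicine ball throw, a plank held to failure, one minute of burpees and a step test.

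Safety is mentioned at several places and with different strength. Conclusions is the firmest: "This study protocol describes an 8-week HIFCT intervention designed to evaluate its feasibility, safety, and potential effects on muscular strength". The Abstract says only that the study may provide "novel evidence regarding the feasibility, safety, and potential effects of HIFCT programmes". The Discussion speaks of examining safety in its opening paragraph and of possibly informing on it in the limitations paragraph. The formal aim and hypothesis at the end of section 1 do not mention safety, and section 2.9 lists no safety outcome.

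**The concern.** The definition ties an adverse event to the time and place of the intervention sessions. Three kinds of occurrence are then not classified as adverse events: anything that happens to a control child, anything in the experimental arm that first shows after the child has left the session, and anything that happens during the post-test assessment in either arm.

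The programme in Table 2 includes tuck jumps, jump squats, jump lunges and externally loaded work, for children who were not in structured extracurricular sport. Pain that builds up or appears later is a plausible harm of such a programme. A child of this age also has ordinary injuries and illnesses over eight weeks, and without a control count there is nothing to set the experimental count against. A reassuring safety statement at the end could then reflect the definition as much as the children's experience.

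**Working it through.** **1. Inputs.** Two sessions a week for 8 weeks, about 50 min each (section 2.8.2). Required sample 46, or 23 per group; recruitment target 52–54, or 26–27 per group (section 2.10). Control children attend no sessions (section 2.8.2). Randomisation follows the baseline evaluations (section 2.4).

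**2. The plan's own figure.** The one design figure is the sample size. A two-sided two-sample t-test with d = 0.86, alpha 0.05 and power 0.80 needs 22.2, rounded up to 23 per group (power 0.814), so 46 reproduces. It was set for VO2max. The article gives no adverse event rate and no safety sample size, and the present point does not rest on 46 except as the number of children.

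**3. Countable exposure under the definition.**
- Sessions per experimental child: 2 × 8 = 16.
- Experimental arm: 23 × 16 = 368 child-sessions, up to 27 × 16 = 432.
- Control arm: 23 to 27 children × 0 sessions = 0.

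The control count is therefore zero whatever happens to those children, and no between-arm contrast exists.

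**4. What a symmetric definition would change.** The documents give no event rate, so the following rates are assumptions. If a proportion b of control children have any event during the study, the chance of seeing at least one is 1 − (1 − b)^n.

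| Assumed b | n = 23 | n = 27 | Under the current definition |
|---|---|---|---|
| 10% | 91% | 94% | 0 |
| 20% | 99.4% | 99.8% | 0 |
| 30% | 99.97% | 99.99% | 0 |

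Across this range a comparator count would almost certainly exist if it were collected.

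**5. What it would not change.** The comparison would still be imprecise. Assuming 10% against 30% of children with an event, power (two-sided 5%, normal approximation) is 39% with 23 per arm and 45% with 27. With 20% against 40% it is 31% and 36%. The table should be read as description with intervals, not as a test.

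**6. Does anything else in the article widen the definition?**
- The Discussion promises systematic monitoring of adverse events throughout the intervention period. It uses the term without redefining it.
- Reasons for missed sessions are recorded (section 2.8.2). This reaches only the experimental arm, only when a session is missed, and not as an adverse event.
- Suspension may follow a medical condition or an adverse event (section 2.8.2). Naming the two separately fits the narrow reading.
- Family reports (sections 2.6 and 2.11) concern activity, diet, sleep and screen time, not injury or pain.

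None of these brings in control children or the post-test session.

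**The case against.** The strongest reply is that safety is secondary here. It is absent from the formal aim, no safety outcome is listed, the Abstract says only that evidence may be provided, and no primary or secondary analysis is affected. That stands and limits the weight of the point. It does not remove it, because Conclusions still presents safety as something the study was designed to evaluate.

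A second reply is that later problems can still come to the team's notice through reasons for absence and the suspension rule. This is also fair: such events are not necessarily unseen, but they are not classified as adverse events, and this route does not exist for controls. One might also read an event arising during participation loosely, so that delayed effects of a session count. Control children and the post-test session would still be excluded.

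Some stronger conclusions are tempting and are not supported:
- A reader might infer that the trial can say nothing about safety. It can describe in-session events in the experimental arm.
- A reader might compute 16 × 50 min = 13.3 h of 8 × 7 × 24 = 1,344 h, about 1%, and infer that nearly all harm is lost. That is a share of clock time, nights and school hours included, and not of risk. The definition covers essentially all supervised exposure, and the documents give no basis for the share of events outside it.
- A reader might note that zero events would exclude only a per-child risk above 1 − 0.05^(1/23) = 12.2%, or 1 − 0.05^(1/27) = 10.5% (one-sided 95%), and blame the definition. The arithmetic is right, but these limits come from the sample size and would be the same under a better definition.

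**Conclusion.** The point holds in a limited form. The article fixes an explicit rule, not a detail left to a fuller document, and the rule gives a one-sided and incomplete harm count: 368 to 432 child-sessions of countable exposure in the experimental arm, none in the control arm, and no classification of events with onset after a session or at post-test. In-session events in the experimental arm can be reported. Comparative safety and the full safety of the programme cannot, and the wording in Conclusions goes further than that. How many events would be left out is unknown, since no event rate is given. The conclusion rests on reading the definition as written and on finding no other text that widens it. The efficacy analyses are untouched.

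**What to change.** Define an adverse event as any injury, pain, illness or other undesirable occurrence from randomisation to the end of post-test, in both arms, and record its relation to a session or to testing as an attribute of the event.

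Keep ascertainment equal. Put the same short questions to families in both arms at the same times, for example once at post-test, and base the between-arm table on that source only, with exact 95% confidence intervals. Report events noted by staff at sessions separately, as a description of the experimental arm. If children in the programme were asked at each of 16 sessions and control families once, adding the two sources together would inflate the experimental count. List events during the baseline tests separately, because they precede randomisation and do not belong in counts by arm.

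If this is not done, limit the safety statements in the Abstract, the Discussion and Conclusions to in-session events in the experimental arm.

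The cost is a short added questionnaire for both arms and one descriptive table. It may need a new form: the activity questionnaire in section 2.3 has no stated post-test administration, and lifestyle changes are recorded only when families report them. The downside is more minor events, reported by parents who know the allocation. The change concerns measurement and reporting only.
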